## Abstract

**Background:**

Multicomponent physical exercise programs are a viable strategy for treating physical decline resulting from the aging process in older populations and can be applied in supervised and home-based modalities. However, the magnitude of the intervention effects in terms of physical function development may vary according to the modalities application due to different supervision degrees.

**Objective:**

This study aims to compare the effects of supervision in a multicomponent exercise program in different application modalities (supervised vs. home vs. supervised+home) in neuromuscular adaptations, muscle strength, gait, physical function, and quality of life, analyzing the differences between intensity, volume, and density of home and supervised sessions in community older adults.

**Methods:**

This protocol is a randomized controlled clinical trial with a sample of 66 older adults divided into three groups: supervised exercise (SUP = 22), home-based exercise (HB = 22), and supervised plus home-based exercise (SUP+HB = 22). The multicomponent exercise program will last 12 weeks, three times per week, for 60 min per session and include warm-up, balance, muscle-strengthening, gait, and flexibility exercises. The study’s primary outcomes will be neuromuscular function, composed of the assessment of muscle isokinetic strength, muscle architecture, and neuromuscular electrical activation. The secondary outcome will be physical function, usual and maximum gait speed with and without dual-task, and quality of life. All outcomes will be assessed at baseline and post-intervention (week 12).

**Conclusion:**

This study will be the first clinical trial to examine the effects of different supervision levels on home-based exercises compared to supervised protocols. The results of this study will be essentials for planning coherent and viable home-based programs for older adults.

**Trial registration:**

Brazilian Registry of Clinical Trials. Number RBR- 7MZ2KR. https://apps.who.int/trialsearch/Trial2.aspx?TrialID=RBR-7mz2kr.

## Introduction

Physical exercise is recommended to prevent or reduce the effects of aging in older people and has been applied in the supervised and home-individual form [1–4]. In general, supervised programs are more effective than home-based programs for improving muscle strength, balance, physical function, and quality of life [3,5]. However, home-based programs are a good option for older adults with limited mobility or who need assistance to go to the training center and have little time for exercise due to family or work responsibilities.

In order to reduce the differences between home-based and supervised programs, recent studies have proposed adding a supervised-group session to home-based programs [6,7]. The addition of supervised-group sessions aims to provide greater exercise supervision, improving the control over frequency, intensity, and progression of exercises, which has been pointed out as one of the main limitations of home-based programs [8]. Nevertheless, control the effect of different supervision levels may directly affect the improvements in older adults’ muscle strength and physical function. However, this hypothesis remains unclear due to the lack of information regarding the impact of different supervision levels in home-based programs.

The indirect supervision of home-based programs may result in limitations in the quality of exercise execution, resulting in exercises with a lower range of motion, less vigorous intensities, and longer rest interval between sets, impairing the exercise effects when compared to supervised training [8]. Thus, the strength gains with resistance exercise are generally associated with a combination of neural and morphological factors, such as increases in muscle mass, reductions in fat infiltration [9], improved firing rate, and decreased antagonist muscle co-activation (Mian., 2006) [10,11], which may not be so effective when performed at home.

To the best of our knowledge, this is the first study that aimed to analyze the neuromuscular mechanisms responsible for improvements in muscle strength and physical function in older adults with the addition of supervised sessions in home-based programs compared to totally unsupervised (home) and supervised training. Thus, we hypothesize that the addition of supervised sessions in home-based programs will lead to greater improvements in neuromuscular mechanisms due to the higher control over the training variables when compared to home-based programs. Besides, we believe that the addition of supervised sessions in home-based programs will provide similar neuromuscular benefits compared to fully supervised training interventions.

Therefore, understanding the influence of different exercise supervision levels on neuromuscular mechanisms and how it may change muscle strength and physical function seems essential for planning coherent exercise programs for older adults, expanding training strategies for that population. Thus, this study had two objectives: Compare the effects of a multicomponent exercise program in different application modalities (supervised vs. home vs. supervised+home) in neuromuscular adaptations, muscle strength, gait, physical function, and quality of life of older adults; and analyze the session intensity, volume, and density of different training modalities (supervised vs. home vs. supervised+home) s in community older adults.

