### Statistical methods

For data analysis, the results will be reported using descriptive statistics and mean and standard deviation. All data will be analyzed by intention-to-treat, with baseline scores substituted for missing follow-up data. The Shapiro-Wilk test will be applied to verify the normality of the data and the Levene test for the sample’s homogeneity. For parametric data, a comparison between groups and periods (pre and post-training) will be analyzed by an ANOVA of mixed-models with Bonferroni’s post-hoc test. When differences between groups were observed at the baseline, a covariance analysis (ANCOVA) will be applied. In addition, a Pearson’s correlation coefficient (r) was calculated to verify the magnitude of the possible observed effects, considering r = .10 as a small effect, r = .30 as a medium effect, and r = .50 as a large effect [34]. P-values less than 0.05 will be considered statistically significant. The tests will be performed using the IBM SPSS Statistics software version 25.

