## Discussion

The present study’s objective is to compare the effects of different supervision levels in a multicomponent exercise program using three different application modalities in muscle strength, gait, physical function, and quality of life, verifying if different training modalities result in different neuromuscular adaptations. Finally, analyze if the addition of supervised sessions in home-based intervention promotes different impacts on the exercise intensity, volume, and density in community older adults.

We hypothesize that adding a supervised session in a home-based program will improve the neuromuscular function (muscle isokinetic strength, quality, and muscle composition), obtaining similar effects to a SUP exercise program, resulting in better effectiveness compared to a strictly HB intervention. It is already known that some factors as quality of exercise execution, range of motion, intensity, the interval between sets, and exercise progression may promote advantages in supervised training sessions compared to home-based interventions. Thus, we believe that the addition of a supervised session in the home-based group will provide direct feedback regarding the intensity, volume, and density of the physical exercise, promoting similar effects in the SUP+HB will be similar to SUP.

Our hypothesis is based on other studies that compared home-based programs with some degree of supervision. In a study conducted by Boshuizen et al. (2005), it was verified that maximal isometric knee strength and the walking speed significantly increase in the group with higher supervision (two group sessions supervised and one unsupervised home session per week) compared to the medium supervision group (one supervised group session and two unsupervised home sessions per week) [35]. Lacroix et al. (2016) found similar results regarding training-related improvements for the Romberg Test, stride velocity, Timed Up and Go Test, and Chair Stand Test in favor of the higher supervised group (two group sessions supervised and one unsupervised home session per week) compared to home-based program (three unsupervised home session per week). Therefore, it is possible to suggest that the addition of supervised sessions can enhance the effects of home-based exercises in older adults.

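### The hypothesis that supervised plus home exercise is similar to full supervision is paired only with a test for a difference, and no stated result could support it

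*Protocol article*

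**What the plan says.** The article states two expectations for the combined arm.

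- **Better than home-based exercise.** The Introduction says that "the addition of supervised sessions in home-based programs will lead to greater improvements in neuromuscular mechanisms" when set against home-based programs.
- **Similar to full supervision.** The Introduction adds that "the addition of supervised sessions in home-based programs will provide similar neuromuscular benefits compared to fully supervised training interventions". The Discussion states both together under its hypothesis, "obtaining similar effects to a SUP exercise program, resulting in better effectiveness compared to a strictly HB intervention", and returns to the second with "promoting similar effects in the SUP+HB will be similar to SUP".

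The similarity statement concerns neuromuscular function, which is the primary outcome domain.

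Statistical methods gives one route to inference: "a comparison between groups and periods (pre and post-training) will be analyzed by an ANOVA of mixed-models with" Bonferroni post-hoc tests, replaced by ANCOVA where groups differ at baseline. The decision rule is "P-values less than 0.05 will be considered statistically significant". Effect magnitude is to be expressed as Pearson's r, "considering r = .10 as a small effect, r = .30 as a medium effect, and r = .50 as a large effect". Analysis is by intention to treat, and a missing week-12 value is replaced by the participant's baseline value. Sample size sets 66 participants, 22 per arm, from an effect size of 0.25.

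**The concern.** A test for a difference can reject equality but cannot confirm similarity. A non-significant SUP+HB versus SUP comparison is what one expects if the arms are alike, and also what one often sees if the combined arm is moderately worse and the sample is small. Two features of the plan push further towards non-significance. Bonferroni adjustment is conservative for the superiority comparison but makes a null result easier to obtain for this pair. Replacing missing follow-up by baseline sets change to zero, which shrinks a between-arm difference when losses are alike across arms.

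At stake is the trial's practical message. The Conclusion section aims at programs for people who have difficulty attending a training site, so whether partial supervision does as well as full supervision is a question that readers will take from the paper. The hypothesis, the test, the decision rule and the sample-size basis are all fixed in this article and do not match, so this is more than a detail left to a later analysis plan.

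**Working it through.** **1. What the sample size was built for.** Inputs from Sample size, as printed: f = 0.25, alpha 0.05, 0.95 (printed as type II error, evidently power), 3 groups, 3 measurements, correlation 0.5, 20% loss. For the group-by-time interaction:

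- λ = f²·N·m/(1−ρ) = 0.0625 × 54 × 3 / 0.5 = 20.25
- df = (3−1)(3−1) = 4 and (54−3)(3−1) = 102
- power = 0.958, and 54 is the smallest multiple of 3 that reaches 0.95
- 54 × 1.2 = 64.8, which gives 66 in three equal arms

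The figure reproduces as an interaction test. The between-groups version would need 168 before loss, and the within version 45. The trial was therefore sized to detect a difference, and no similarity criterion enters.

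**2. Precision for SUP+HB versus SUP.** With n = 22 per arm, in SD of change:

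- standard error = √(2/22) = 0.3015, df = 42
- 95% half-width = 2.018 × 0.3015 = 0.61 SD
- at alpha 0.05/3: 2.494 × 0.3015 = 0.75 SD

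**3. Chance of a non-significant result when the combined arm is truly worse.** Noncentral t with noncentrality d/0.3015. The deficits d are assumptions, because the article gives neither an SD nor a margin.

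| True deficit (SD of change) | Unadjusted | Bonferroni, 3 pairs |
|---|---|---|
| 0.3 | 84% | 92% |
| 0.5 | 63% | 79% |
| 0.8 | 26% | 43% |
| 1.0 | 10% | 21% |

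Using the error term pooled over all three arms (63 df) gives 63% and 78% at 0.5 SD, so the two-arm simplification does not matter.

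**4. Effect of the missing-data rule.** Baseline substitution keeps all 22 per arm in the analysis. With an assumed 20% random loss in each arm, the expected difference shrinks from 0.5 to 0.8 × 0.5 = 0.4 SD. Simulating this rule with a mean change in SUP of 0.5 to 1.0 SD gives non-significance in about 70–72% of trials, and about 84–86% with Bonferroni.

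**5. What a similarity test could deliver.** Non-inferiority, one-sided 0.025, true difference zero, margins assumed:

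| Margin (SD) | Evaluable n per arm for 80% power | Power at 22 per arm |
|---|---|---|
| 0.3 | 175 | 16% |
| 0.5 | 63 | 37% |
| 0.8 | 25 | 74% |

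**The case against.** The strongest reply is that the plan never says how p>0.05 will be interpreted. The stated objectives are to compare the modalities and to analyze session intensity, volume and density. Neither is an equivalence objective, and the Introduction offers similarity as a belief. This stands in part. A reader might infer that the investigators intend to read non-significance as similarity, but the article does not say so. What remains is that the similarity hypothesis appears in both the Introduction and the Discussion and has no result that could support it.

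A reader might also take the article's own evidence to point to a deficit. The Discussion cites a study in which strength and walking speed favoured the more supervised group "compared to the medium supervision group (one supervised group session and two unsupervised home sessions per week"), which is the SUP+HB schedule. But the comparator there had two supervised sessions and one home session, so it was not this trial's SUP arm. The Discussion also cites a meta-analysis in which the advantage of supervision could shrink or vanish once some supervision was added to home programs. The cited evidence is mixed.

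A third tempting reading is that Pearson's r is undefined here. It is not: r can be derived from t and its degrees of freedom for a single pairwise contrast, and the plan does not tie it to the overall interaction. The valid point is narrower: r with small, medium and large labels gives no interval for the difference between arms.

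Finally, one might compute precision from 17 or 18 per arm after 20% loss. That would not describe the stated analysis, which retains everyone by substitution.

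**Conclusion.** The point holds. As stated, the analysis cannot support the hypothesis that SUP+HB is similar to SUP, because it contains only a test for a difference and no criterion for similarity. With 22 per arm, a true deficit of 0.5 SD of change would go undetected in about 63% of trials (79% with Bonferroni). The figure depends strongly on the assumed deficit: from 84% (92%) at 0.3 SD to 10% (21%) at 1.0 SD. A non-significant result would leave differences of roughly 0.6 SD around the estimate open.

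These figures assume roughly normal change scores with equal variance in the arms. Step 4 also assumes random loss at an equal rate.

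The defect does not touch the superiority hypothesis against HB or the descriptive objectives, and harm arises only if a null result is later overread. It should be fixed before analysis but does not undermine the trial as a whole.

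**What to change.** In Statistical methods:

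- Report the baseline-adjusted mean difference, SUP+HB minus SUP, with its 95% CI, and do the same for the other two pairs. Pearson's r may stay as a supplement.
- State that p>0.05 for SUP+HB versus SUP will not be interpreted as similarity.
- Claim similarity only if a margin, justified and fixed in advance on one named primary variable, is excluded by the CI. Otherwise present the comparison as estimation and word the hypothesis in the Introduction and Discussion to match.

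The first two changes are wording and cost nothing in data collection. The third costs more: the primary outcomes list many variables and single out none, so one would have to be chosen. A formal test would also have little power at the present size, about 37% at an assumed margin of 0.5 SD, where 80% power would need 63 evaluable per arm. Without enlargement, the honest answer on similarity will probably be inconclusive, and the plan should say so.

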## Materials and methods

### Trial design

It is a protocol for a randomized controlled clinical trial, investigator-blinded, with three parallel groups. Participants are individually randomized to one of the three groups in a 1:1:1 allocation ratio. The Research Ethics Committee approved the project at the Federal University of Paraná, Brazil (UFPR) (CAAE:20181219.4.0000.0102). The study protocol was developed based on the Standard Protocol Items: Recommendations for Interventional Trials (SPIRIT) guidelines [12]. The study follows the CONSORT guidelines [13], and all the items from the World Health Organization Trial Registration Data Set were registered in the publicly accessible Brazilian Registry of Clinical Trials (RBR-7MZ2KR). Any change made to the protocol will be reported to the Research Ethics Committee and modified in the Brazilian Registry of Clinical Trials.

The enrolled participants’ assessments will be carried out at baseline prior to randomization, and after three months, as described below (Fig 1).

**Fig 1 pone.0259827.g001:**
[figure not shown]
Schematic representation of participant recruitment and allocation.

### Study setting

The study will be carried out in the city of Curitiba, Paraná, Brazil. In Paraná, the older population increased by 15.92% in the last five years, totaling 1.717.889 people [14]. In 2017, Curitiba registered 268.700 people aged over 60 years old. According to population projection assumptions, the number of older adults in Curitiba is expected to rise to 432.500 in 2030 and 544.500 in 2040.

### Eligibility criteria

The inclusion criteria will be: men and women aged > 60 years; be able to perform basic daily activities; not engaged in structured physical exercise program (previous six months); without cognitive impairment determined through the Mini-Mental State Examination [15].

Exclusion criteria include physical or motor limitations that make it impossible to perform functional tests; recent history of stroke or heart failure; uncontrolled acute or chronic metabolic disorders; severe osteoporosis; two or more fractures in the last year; medical contraindications for participation in an exercise program.

The participants will not be allowed to participate in another physical protocol concurrently with the present study.

### Recruitment, randomization, and treatment allocation

The study will be carried out in Curitiba, Paraná, Brazil. Volunteers will be recruited by dissemination through digital media (local digital newspaper and Facebook) and health units.

After checking the inclusion and exclusion criteria and analyzing the screening/anamnesis, the volunteers will sign a Free and Informed Consent Form. The participants will then be randomized by blocks into one of the three groups of equal size by a researcher who is not involved in the study. The randomization will be made at the randomization.com website. A second researcher not involved in the study will receive an envelope with the participants’ allocation, contacting them to inform them about their specific training group. The researchers who carry out the evaluations and interventions will be blinded to the distribution of the groups.

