### Intervention groups

Volunteers will participate in a multicomponent exercise program combining supervised and home-based exercise for 12 weeks, three times per week, 60 min per session. Participants will be divided into (1) supervised exercise (SUP), who will attend supervised group sessions at the training center; (2) home-based exercise (HB), who will participate in individual sessions at home; (3) supervised plus home-based exercise (SUP+HB), who will attend to one session per week at the training center and two sessions per week at home. Physical educators or physiotherapists will guide the supervised sessions at the training center.

The volunteers who will attend home sessions (HB and SUP+HB) will have an initial visit to their home to receive recommendations about how to perform the exercises safely. A guide with illustrations and instructions to reinforce proper exercise execution will be provided to each participant with space for recording the sessions performed and possible occurrences. On this occasion, they will receive ankle cuff weights (1, 2 and, 4 kg) to the strength training and a square stepping for walking exercises. To control program adherence, participants will record the days they complete the program, and they will also receive messages with incentives to perform the exercises at home.

The exercise program will consist of functional exercises of muscle strength, balance, flexibility, and gait, based on the recommendations of Singh et al. [16] and American College of Sports Medicine [17] (ACSM). Each session will be divided into 05 minutes of dynamic and articular warm-up, 10 minutes of dynamic and static balance exercises, 25 minutes of muscle-strengthening exercises, 10 minutes for gait exercises, and 10 minutes of flexibility exercises.

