### Measurements

The evaluation sessions will be conducted in the biomechanics laboratory in CECOM at UFPR, where trained evaluators will administer the tests. The evaluators responsible for applying the exercise program will not participate in evaluating the sample, aiming to guarantee a simple blind study. The steps and timeline of the assessments can be observed in Fig 2.

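### The article says that staff who deliver the interventions are blinded to group; in a trial whose arms differ by supervision, only the outcome assessors can be

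*Protocol article*

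**What the plan says.** Three places in the protocol article describe blinding.

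- **Trial design:** "It is a protocol for a randomized controlled clinical trial, investigator-blinded, with three parallel groups". The role covered by the word investigator is not given.
- **Recruitment, randomization, and treatment allocation:** after describing block randomization by an uninvolved researcher, and a second uninvolved researcher who holds the envelope and tells participants their group, the section ends: "The researchers who carry out the evaluations and interventions will be blinded to the distribution of the groups".
- **Measurements:** "The evaluators responsible for applying the exercise program will not participate in evaluating the sample, aiming to guarantee a simple blind study".

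The Intervention groups section defines the arms. SUP are those "who will attend supervised group sessions at the training center", HB are those "who will participate in individual sessions at home", and SUP+HB are those "who will attend to one session per week at the training center and two sessions per week at home". The programme runs three times per week for 12 weeks in every arm. On staffing: "Physical educators or physiotherapists will guide the supervised sessions at the training center". Participants in HB and SUP+HB, but not SUP, have an initial visit at home, at which they receive instructions, ankle weights and a square-stepping aid.

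**The concern.** In this trial supervision is the treatment. Someone who supplies it sees how much of it a participant receives, so a statement that those carrying out the interventions are blinded describes something the design cannot provide. It is a positive claim, not a detail left to a fuller document.

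What is at stake is how the results are later judged. A risk-of-bias assessment or a final report that takes the sentence at its word would record blinded personnel. The article hypothesizes that adding supervised sessions will do better than home training alone, so staff expectations could run in a known direction. Several outcomes depend on voluntary effort or self-report. The limitation named in the Discussion concerns spontaneous physical activity; non-blinding of trainers and participants is not mentioned there.

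**Working it through.** No figure in the plan depends on this point, so there is nothing to recompute. The check sets the blinding statements against the delivery of each arm.

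**Step 1. What staff see in each arm** (inputs from Intervention groups; group sizes from the Abstract)

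| Arm | Planned n | Supervised center sessions over 12 weeks | Initial home visit |
|---|---|---|---|
| SUP | 22 | 3 × 12 = 36 | no |
| SUP+HB | 22 | 1 × 12 = 12 | yes |
| HB | 22 | 0 | yes |

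**Step 2. What a center trainer can infer.** Anyone in a supervised session is not in HB. Attendance three times a week points to SUP and once a week to SUP+HB. The article does not say whether the two arms train together. If they train apart, the session itself shows the arm; if together, the attendance pattern does. This applies to 22 + 22 = 44 of the 66 planned participants.

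**Step 3. What a home visitor can infer.** Anyone visited is not in SUP. This again applies to 22 + 22 = 44 of 66 participants, those in HB and SUP+HB. Between them, the two kinds of staff contact cover all 66.

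**Step 4. What participants know.** The recruitment section says that they are told their training group. The article nowhere calls them blinded.

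**Step 5. What assessors can be kept from knowing.** Baseline tests take place before randomization, so the arm does not yet exist. At week 12 the tests are run by people who did not deliver the programme. Blinding is feasible for them, provided that they do not see the allocation list and participants do not tell them.

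**Step 6. The three statements side by side.** The recruitment section blinds both assessors and deliverers. The Measurements section offers the separation of the two roles as the means of achieving single blinding, which is most naturally read as trainers knowing the arm and assessors not. The Trial design section fits either version. Steps 2 and 3 rule out the deliverer part of the recruitment sentence, which leaves assessor blinding as the version consistent with the design.

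**Step 7. Which outcomes are exposed.**

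- *More exposed, voluntary effort:* isokinetic strength and maximal voluntary isometric contraction (primary), and gait at maximum speed (secondary).
- *More exposed, self-report:* SF-36 (secondary).
- *Less exposed:* muscle architecture from resting ultrasound and the electrically evoked twitch measures, which belong to the primary set.

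**The case against.** The best defence is that the sentence is loosely worded. It closes a paragraph on allocation, and being blinded to the distribution of the groups may mean only that study staff have no access to the allocation list. The document also already contains the protection that matters, because trainers do not assess. Unblinded trainers are unavoidable in any trial of supervision, and no analysis or sample size changes.

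Part of this stands. The fault is one of wording, and the separation of roles is sound. But concealment is already covered by the sentences on the uninvolved researchers and the envelope, whereas the disputed sentence says blinded and names those who carry out the interventions. As written it is untrue.

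Several stronger readings are tempting and are not supported:

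- **That the investigator-blinded label is false.** It is ambiguous. If it means the assessors, it is correct.
- **That the Measurements section flatly contradicts the recruitment section.** Separating two roles does not exclude blinding both. The tension is an inference from the stated aim of a single-blind study.
- **That outcome assessors are unblinded.** Nothing in the document shows this.
- **That the article hides participants' knowledge of their group.** It says openly that they are told. Bias in SF-36 answers would come from that knowledge, not from the sentence about researchers.
- **That the primary outcomes are all effort-dependent.** Gait and SF-36 are secondary, and the primary set includes resting ultrasound and evoked responses.
- **That encouragement might differ by group.** Verbal commands are mentioned only for isokinetic testing, where they distinguish the submaximal familiarization test from the maximal recorded test.

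**Conclusion.** The point holds as a wrong statement about who is blinded. Those who deliver the interventions cannot be blinded in this design; outcome assessors can be, and the Measurements section implies that they are the ones meant. The Trial design label needs its role named.

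The size is modest. No sample size, alpha, power figure or analysis changes. Staff contact that reveals or narrows the arm reaches all 66 planned participants, but the direction and amount of any bias in the results cannot be quantified from the document. The consequence is an overstated protection against performance bias, most relevant to the voluntary-effort tests. SF-36 belongs in the same limitation because participants know their group.

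The conclusion rests on the arms being delivered as the Intervention groups section describes, and on the assessors being different people from the trainers, as the Measurements section says. The correction should be made, but it does not call the design into question.

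**What to change.** 1. In the recruitment, randomization and treatment allocation section, limit the blinding sentence to outcome assessors, and state that trainers and participants are not blinded.
2. In the Trial design section, replace investigator-blinded with assessor-blinded, so that it agrees with the Measurements section. That section needs no change on this point.
3. In the Discussion, list non-blinding of trainers and participants as a limitation. Say that it bears mainly on isokinetic strength, maximal isometric contraction, gait at maximum speed and SF-36, and less on resting ultrasound and evoked-twitch measures.
4. Keep the allocation list from assessors, and instruct participants not to disclose their group at the post-intervention tests. The article is not at fault for omitting such operational detail, but these steps protect the only blinding that is achievable.
5. Do not add that the data analyst is blinded unless that is so; the article is silent on it.

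The cost is a change of wording in two sections, an added limitation and one instruction to participants. The stated blinding becomes less favourable. Arms, outcomes, sample size and analysis stay as they are.
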